The study will be conducted at private volleyball clubs located in Nilai and Subang, Malaysia. Ethical approval has been obtained from the University Research and Ethics Panel with ref. no. INTI-IU/FHLS-RC/BPHTI/1NY12025/007 and adhered to the declaration of Helsinki. This non-randomized matched controlled study has been registered with ClinicalTrials.gov (NCT07485348). The exercise intervention will be delivered by a sports physiotherapist who had over 10 years of experience in the relevant field. All participants will be briefed about the study's objectives and procedures. The participation of the subjects in this study will be voluntary, and each participant would be expected to sign the informed consent form before participation. Subjects will be allowed to discontinue from the study if they experience any form of musculoskeletal injury or any adverse effects observed during the delivery of the intervention. Any form of harm during the session will be documented through observation and self-reporting measures.

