### Sample size and participants

The target population will be comprised of male volleyball players aged 18 to 25 years, with a minimum of one year of continuous playing experience at university level, playing position setter, hitter, blocker, a training frequency of at least twice per week with minimum weekly training volume of 3 h, previous lower limb injury status will be collected. Individuals who had sustained a recent lower-limb injury or undergone surgery within the past six months, individuals with neurological or vestibular diseases, or participants involved in other structured training programs will be excluded. This selection guaranteed a uniform athletic background among participants. LESS, anthropometric measures, and body composition will be considered as primary outcomes, and vertical jump height will remain as a secondary outcome. Sample size has been calculated using G*Power (version 3.1.9.4) based on effect sizes obtained from research conducted by Pfile et al., which demonstrated a significant change in LESS after 6 weeks of NMT (F^2^, ^10^ = 6.29, *p* = 0.009) providing a partial eta square (*η*^2^p) of 0.557 and cohen's f of 1.12 (27). However, this study utilized single-group repeated measures instead of a controlled trial, and a more cautious interaction effect size (f = 0.25) was computed using ANCOVA, adjusted for baseline/linear mixed-effects model. Secondary outcome *p*-values will be adjusted for multiplicity, using the Holm-Bonferroni method with a significance level of *α* = 0.05 and statistical power of 0.8, which necessitated a minimum of 28 participants (14 per group). The total recruiting target will be established at 31 athletes to account for a probable 10% dropout. This sample size calculation has been performed considering the primary outcome only; results regarding secondary outcomes should be considered exploratory.

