### Jump height

Vertical jump height will be determined using the Vertec jump tester, a reliable field-based device widely used in sports performance assessments. The Vertec has demonstrated strong correlation with force-platform and flight-time methods (r = 0.86–0.93) and high test–retest reliability (ICC = 0.73–0.99). Participants’ standing reach height will be measured first, followed by three maximal countermovement jumps separated by two-minute rest intervals. The highest vane displaced will be recorded and used for analysis. Although the Vertec may produce slightly higher readings than force-platform measures, it remains a consistent and valid tool when standardized protocols are followed (30).

Data collection will be conducted at two time points: pre-test (baseline) and post-test (after eight weeks). Participants will complete the demographic questionnaire covering age, training history, injury background, and weekly training frequency. All assessments will be conducted under identical conditions by a trained assessor who will be blinded about group allocation to maintain measurement consistency. Each test will be interspersed with a standardized two-minute rest period to mitigate tiredness. Data confidentiality will be rigorously maintained during the investigation. The order of testing will follow the sequence for all participants: Demographic questionnaire, anthropometric and body composition measures, the jump-landing assessment, and then the vertical jump height testing. Unique participant identification numbers will be used to code the data for confidentiality and for effective data management. Measurement procedures will be standardized, with calibrated instrumentation and the same environmental setting. Further, blinding the assessor to the group allocation, and uniform verbal instructions, will be used to reduce measurement bias. Recorded data will also be randomly checked to ensure accuracy and completeness.

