## Intervention protocol

The intervention for both groups will have a matched warm up and cool down phase of 10 min and 5 min respectively along with 45 min of structured exercise protocol, a 1-minute rest interval will be provided between each set for both groups. The intervention regimen for the experimental group comprised an 8-week structured neuromuscular training program conducted thrice a week, in conjunction with regular volleyball practice. Each 60-minute session will commence with a 10-minute dynamic warm-up that incorporated mobility and stretching exercises, including lunges with trunk rotation, leg swings, and jogging. Borg scale of rate of perceived exertion (RPE) will be used to prescribe the exercise intensity for both groups. The exertion level will be maintained between 13 and 16 (somewhat hard to hard). RPE will be recorded after each training session and utilized to guide progression when appropriate. Training load during each session will be closely monitored through RPE method (session × perceived exertion score). The primary training phase will include 45 min of incremental neuromuscular activities aimed at improving proprioception, balance, and lower-limb control. In the initial four weeks (Foundation phase), participants will be instructed to execute bodyweight squats, bilateral stance on BOSU ball, unilateral stance with contralateral leg swing, Jump and freeze, Lateral bounds, Single Leg Romanian Deadlift. Progression of the training load will be implemented every 4 weeks by modifying exercise complexity, balance challenge, repetitions and external resistances. Each progression will be allowed only when participants performed correct technique without any compensatory movement patterns during two consecutive sessions. The training intensity and complexity will be incrementally elevated from weeks five to eight (Advanced neuromotor phase) through the incorporation of barrier Jump front cone runs, Single leg hops (lateral + forward) and Zig-zag cone drills, Single Leg Romanian Deadlift. A one-minute rest interval will be provided between sets, and each session will be concluded with a 5-minute cool-down comprising light jogging and static stretching [EG training Protocol is specified in Table 1]. In contrast, the CG will continue their routine volleyball training supplemented with a structured resistance-training program over the same period. Approximately 60 min per session [CG training Protocol is specified in Table 2]. This design will ensure that any observed differences between groups could be attributed to the neuromuscular component rather than general training volume or duration. The training protocol for EG will be adopted and modified from the previous studies (31–33). The training regimen for CG will be derived from validated earlier protocols in volleyball specific conditioning studies (34, 35). Participants will be instructed not to engage in any other structured interventions that are designed to improve body composition and movement patterns during the intervention session. To maintain the fidelity, all the sessions will adhere to a standard training manual, consistent exercise sequence, progression timeline. All training sessions will be conducted at the indoor volleyball training facility centre equipped with a suitable training surface, and the intervention will be closely supervised by the qualified sports physiotherapist to ensure proper exercise execution, deliver feedback and minimize injury risk. A 85% regular attendance rate will be mandatory to comply with the intervention protocol. Adverse events such as musculoskeletal strain, sprains or any other form of sports related incidents will be recorded and reported to ethical committee by the principal investigator throughout the study. In addition, upon completion of the intervention protocol, all outcome parameters will be measured immediately on the same day using a randomized test sequence for all groups, with the same investigator being assigned to collect data to avoid bias of the assessor between the pre- and post-intervention period in the same environment.

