### Data analysis

Data will be analysed using SPSS version 29.0 (IBM Corp., Armonk, NY, USA). Descriptive statistics will be presented as means and standard deviations for all dependent variables. Multiple imputation analysis will be implemented to evaluate the robustness of the findings. The primary analysis will be a group × time interaction test performed using ANCOVA, adjusted for baseline/linear mixed-effects model (LME), and will report effect sizes and 95% CIs for all outcomes. Secondary outcome *p*-values will be adjusted for multiplicity, using the Holm-Bonferroni method. The primary analysis population will be the intention-to-treat population, with multiple imputation to handle missing follow-up data, and a per-protocol analysis (at least 85% session attendance) will be conducted as a sensitivity analysis. Treatment group, assessment time points, baseline levels of all outcome measures, demographic variables (age, body mass index), and missingness and/or outcome measure related variables will be part of the imputation model. Sensitivity analyses will be conducted to assess the robustness of the findings: (1) multiple imputation ITT analysis, (2) complete case analysis, and (3) per protocol analysis (attending ≥85% of intervention sessions).

The principal researcher and the team will frequently monitor the subject's safety, adherence to protocol, data collection. No interim analysis will be implemented as the study will be investigated throughout the intervention period. Furthermore, data monitoring committee will not be formed for this study, as the study involves shorter duration, non-invasive outcome measurements and relatively low-risk intervention. However, safety of the participants will be closely monitored by the principal investigator and the team throughout the study period. Any adverse events, injuries during the intervention will be documented, managed and reported to ethics committee if required.

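### A player who stops training after injury may leave the study unmeasured, because the protocol does not separate stopping training from leaving follow-up and times the post-test in two different ways

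*Protocol article*

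**What the plan says.** **Exit.** Study design & ethical approval gives one route out after harm: "Subjects will be allowed to discontinue from the study if they experience any form of musculoskeletal injury or any adverse effects". Nothing in the article says that a player who stops training will still be asked to attend the post-test.

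**Timing of the post-test.** The Jump height section sets it by time: "Data collection will be conducted at two time points: pre-test (baseline) and post-test (after eight weeks". The Intervention protocol section sets it by an event: "upon completion of the intervention protocol, all outcome parameters will be measured immediately on the same day".

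**Attendance.** Intervention protocol: "A 85% regular attendance rate will be mandatory to comply with the intervention protocol".

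**Analysis.** Data analysis: "The primary analysis population will be the intention-to-treat population, with multiple imputation to handle missing follow-up data". The sensitivity analyses are listed as "1) multiple imputation ITT analysis, (2) complete case analysis, and (3) per protocol analysis (attending ≥85% of intervention sessions". The imputation model takes group, time point, baseline outcomes, age and BMI, and adds that "missingness and/or outcome measure related variables will be part of the imputation model". Injury is not named.

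**Expected loss.** Sample size and participants: "The total recruiting target will be established at 31 athletes to account for a probable 10% dropout".

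**The concern.** An intention-to-treat analysis is only as good as the follow-up of players who depart from the plan. For a player who completes eight weeks, the two timing statements coincide. For a player who stops in, say, week 3, the calendar statement makes a week-8 measurement due, while the completion statement supplies no occasion for one. Add an exit rule worded as leaving the study, and a site can follow the text and collect nothing further from that player.

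The loss would not be neutral. Landing quality (LESS) is a primary outcome, and the Introduction itself links landing mechanics to injury. The arms train differently: Table 1 has bounds, hops and box jumps, and Table 2 has mainly barbell, dumbbell and machine work. Injury-related loss could therefore depend on the unseen outcome and differ by arm. If injured players would have scored worse than imputed, the arm that loses more of them looks better than it should.

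Part of the loss is avoidable. The section on anthropometric profile and body composition lists body fat percentage, lean mass percentage, total body water, BMI and waist–hip ratio. These belong to the primary outcomes and none needs a jump.

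**Working it through.** **1. The plan's own dropout figure.** Inputs are a minimum of 28 players and 10% dropout. 28 × 1.10 = 30.8, which rounds up to the stated 31. (28 / 0.90 = 31.1 would round up to 32; the one-player difference does not affect this point.) The allowance is therefore 31 − 28 = 3 players, and 3/31 = 9.7%.

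**2. What each passage implies for a player who stops early**

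| Passage | Is a week-8 measurement due? |
|---|---|
| Study design: may discontinue from the study | Not if the player takes the option |
| Jump height: post-test after eight weeks | Yes |
| Intervention protocol: post-test on completion | No trigger, if read player by player |
| Data analysis: intention-to-treat is primary | The player counts; a missing value is imputed |

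**3. Why imputation does not settle it.** The model may include missingness-related variables, so injury could enter. But if the players who leave after injury have no post-test values, they contribute nothing from which the effect of leaving injured can be estimated, and their values are predicted from players who stayed. Of the three listed sensitivity analyses, the first repeats the primary analysis. The other two are complete case and per protocol. None varies the missing-at-random assumption.

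**4. Size (assumed values, since the protocol gives none).** Let p be the share of an arm with imputed post-test values, and s the amount, in SD, by which the true values are worse than imputed. The bias in that arm's mean is p × s.

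| p | s = 0.5 SD | s = 1.0 SD |
|---|---|---|
| 10% | 0.05 | 0.10 |
| 20% | 0.10 | 0.20 |

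The 20% row corresponds to all three allowed losses falling in one arm: 3/16 = 18.75% or 3/15 = 20%. With s = 1.0 SD that gives 0.19–0.20 SD.

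The bias in the group difference is (p × s) in one arm minus (p × s) in the other. With three losses split as evenly as possible and s = 1.0 SD in both arms, it is 2/16 − 1/15 = 0.058 SD, or 2/15 − 1/16 = 0.071 SD. With equal shares and equal s it is zero.

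**5. Against the planned effect.** The protocol calls f = 0.25 an interaction effect size. With two groups and two time points, interaction f corresponds to a difference in change of 4f = 4 × 0.25 = 1.0 SD. On this reading N = 28 gives power 0.813 if the pre–post correlation is 0.6 (not stated in the protocol). Then 0.19/1.0 = 19%. If f is instead read as a between-group ANCOVA effect, the difference is 2f = 0.5 SD and 0.19/0.5 = 38%. On that reading 28 players suffice only at a correlation of 0.9. The protocol names both analyses, so the ratio is not fixed.

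**6. The attendance rule.** 8 weeks × 3 sessions = 24, and 0.85 × 24 = 20.4, so 21 sessions are needed; 20/24 = 83.3% falls short. Missing four sessions puts a player below the line. Data analysis uses that line only to define the per-protocol set.

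**The case against.** The best reply is that the text removes nobody. Discontinuing is permitted, in a paragraph about voluntary participation, and nothing bars an injured player from the post-test. The completion wording can be read as the end of the eight-week programme for all groups, in which case the two timing statements agree. The attendance rule carries no exclusion. A per-protocol analysis listed separately from the complete-case analysis presupposes that some players below 85% are measured. Imputation is planned only for missing follow-up, so observed values are already used. The article does not attribute its 10% dropout to injury. And a condensed article may leave follow-up of players who stop to a fuller document.

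Most of this stands, and it rules out some tempting inferences. A reader might infer that injured players are withdrawn, or that the intention-to-treat set must shrink to completers plus imputed values. The text permits such losses but does not require them. Nor does the 85% rule itself cause missing data.

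What does not fall away is the stated wording: an exit phrased as leaving the study, and two post-test timings that part company for exactly the players on whom an intention-to-treat analysis depends. That is an ambiguity in what the article says, not merely something it leaves out.

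**Conclusion.** The point holds as a weakness of wording with a plausible effect on bias. Injured players may go unmeasured and be represented in the primary analysis only by values imputed from others, with no planned check on departure from missing at random.

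The size is illustrative: 0.05–0.20 SD in one arm's mean, assuming 10–20% of that arm is lost and those players are truly 0.5–1.0 SD worse than imputed. The upper end needs all three allowed losses in one arm, each about 1 SD worse. Near-even losses leave little bias.

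A reader might put the upper-end bias at 38% of the planned effect. The documents do not support that as a firm figure: it needs the ANCOVA reading of f, and the interaction reading that the protocol names gives about 19%.

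The change is worth making because it is cheap and prevents a loss that analysis cannot reliably repair. Whether an injured player trains or jumps is a clinical matter on which no view is given here.

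**What to change.** - **Study design & ethical approval:** separate stopping the training programme from withdrawing from follow-up. Keep the right to withdraw from either at any time.
- **Jump height and Intervention protocol:** reconcile the two timings so that the post-test falls at week 8 by calendar for every allocated player who still consents, whether or not training was completed.
- **Where the jump tests are not done:** collect at least the impedance and anthropometric measures, and record why the jump tests are missing.
- **Data analysis:** state that post-test values observed after a player stops training are used in the intention-to-treat analysis, with imputation only for what remains missing. This reduces how much rests on the missing-at-random assumption but does not remove it.
- **Attendance:** align the mandatory 85% wording in Intervention protocol with Data analysis, where 85% only defines the per-protocol set.

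The cost is a wording change in the protocol and consent form, some chasing of players who stopped, and a slightly diluted effect estimate, because players with partial training contribute their real outcomes. The week-8 assessment is already planned, so no new visit is added.

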### Sample size and participants

The target population will be comprised of male volleyball players aged 18 to 25 years, with a minimum of one year of continuous playing experience at university level, playing position setter, hitter, blocker, a training frequency of at least twice per week with minimum weekly training volume of 3 h, previous lower limb injury status will be collected. Individuals who had sustained a recent lower-limb injury or undergone surgery within the past six months, individuals with neurological or vestibular diseases, or participants involved in other structured training programs will be excluded. This selection guaranteed a uniform athletic background among participants. LESS, anthropometric measures, and body composition will be considered as primary outcomes, and vertical jump height will remain as a secondary outcome. Sample size has been calculated using G*Power (version 3.1.9.4) based on effect sizes obtained from research conducted by Pfile et al., which demonstrated a significant change in LESS after 6 weeks of NMT (F^2^, ^10^ = 6.29, *p* = 0.009) providing a partial eta square (*η*^2^p) of 0.557 and cohen's f of 1.12 (27). However, this study utilized single-group repeated measures instead of a controlled trial, and a more cautious interaction effect size (f = 0.25) was computed using ANCOVA, adjusted for baseline/linear mixed-effects model. Secondary outcome *p*-values will be adjusted for multiplicity, using the Holm-Bonferroni method with a significance level of *α* = 0.05 and statistical power of 0.8, which necessitated a minimum of 28 participants (14 per group). The total recruiting target will be established at 31 athletes to account for a probable 10% dropout. This sample size calculation has been performed considering the primary outcome only; results regarding secondary outcomes should be considered exploratory.

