**Methods:**

This non-randomized matched controlled study will utilize 28 male volleyball players aged between 18 and 25 years. Following baseline assessment, participants will be allocated to experimental group (INMT along with volleyball training) and control group (volleyball training along with a structured resistance training program) using non-randomized allocation procedure and a set of predefined criteria. The intervention will last 8 weeks, with three sessions per week. Primary outcome parameters such as body composition, anthropometric profiles, landing kinematics will be assessed using bioelectrical impedance analysis and landing error scoring system. The secondary outcome, vertical jump height, will be analyzed using vertec jump tester respectively. Group × time interaction test will be computed using ANCOVA, adjusted for baseline/linear mixed-effects model. Secondary outcome *p*-values will be adjusted for multiplicity, using the Holm-Bonferroni method.

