## Outcome parameters

### Anthropometric profile and body composition

The anthropometric profile will be assessed utilizing a Bodystat 1500MD bioelectrical impedance analysis (BIA) instrument, which quantifies body composition metrics including body fat percentage, lean mass percentage, total body water (TBW%), BMI, and waist–hip ratio (WHR). Bioelectrical impedance analysis (BIA) is a non-invasive and dependable technique for evaluating body composition, exhibiting moderate to high reliability (ICC = 0.67–0.99) and validity in estimating fat-free mass within athletic populations (28). Nevertheless, given that hydration, ethnicity, and sex can affect impedance measurements, all participants will be directed to sustain normal hydration, refrain from vigorous activity for a minimum of 48 h and follow their customary diet before testing. Participants will complete a standardized pre-assessment questionnaire before each assessment to ensure that they will be well-hydrated, will avoid intensive exercise for 48 h prior to the assessment, and will maintain their normal food intake. Compliance will be verbally verified by the investigator before testing. Weight and height will be assessed with a calibrated stadiometer, and BMI will be computed appropriately.

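### The only multiplicity correction covers a secondary family of one outcome, while the several primary outcomes share one alpha of 0.05 with no split, order or success rule

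*Protocol article*

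**What the plan says.** Under Sample size and participants, the protocol article sets the outcome hierarchy: "LESS, anthropometric measures, and body composition will be considered as primary outcomes, and vertical jump height will remain as a secondary outcome". The Methods abstract agrees, with "Primary outcome parameters such as body composition, anthropometric profiles, landing kinematics will be assessed" on one side and "The secondary outcome, vertical jump height, will be analyzed using vertec jump tester" on the other.

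The section Anthropometric profile and body composition lists what the impedance device measures: "body fat percentage, lean mass percentage, total body water (TBW%), BMI", followed by waist–hip ratio. It adds: "Weight and height will be assessed with a calibrated stadiometer, and BMI will be computed appropriately".

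On multiplicity, Data analysis says that secondary-outcome p-values "will be adjusted for multiplicity, using the Holm-Bonferroni method". The Methods abstract and the sample-size section limit the correction in the same way. Alpha is given once, as 0.05, in the sample-size section.

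That section takes its starting effect size from an earlier study of LESS, says "This sample size calculation has been performed considering the primary outcome only", and describes secondary results as exploratory. No section gives an alpha split, a testing order, a lead outcome or a rule on how many primaries must succeed.

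**The concern.** A multiplicity correction is needed where several tests can each support the main claim. Here it is attached to the one family that cannot need it, because that family has a single member and is labelled exploratory. The primary set, which does hold several outcomes, gets no correction and no rule for reading mixed results.

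A reader of the final report could not tell whether the trial succeeded if, say, body fat percentage moved and LESS did not. The stated 0.05 may then not be the error rate of the main conclusion.

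This is more than a detail left to a statistical analysis plan. The protocol names the method and its scope in three places. An analysis plan that follows the protocol inherits the problem, and one that departs from it contradicts the protocol.

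**Working it through.** **Inputs from the protocol article**
- Primary domains: 3 (LESS, anthropometric measures, body composition).
- Named body metrics: 5 (body fat %, lean mass %, total body water %, BMI, waist–hip ratio). With the LESS score this makes 6 variables. Weight and height are measured but are not clearly endpoints, so they are left out.
- Secondary outcomes: 1 (vertical jump height).
- Alpha 0.05, power 0.8, f = 0.25, N = 28 (14 per group), two time points.

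**Assumed:** the correlation between primary test statistics (0 to 0.7), and the within-person correlation rho in the power formula. The protocol gives neither.

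**1. The planned correction.** Holm compares the smallest of m p-values with 0.05/m. With m = 1 this is 0.05/1 = 0.05, so nothing changes.

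**2. Family-wise error if any significant primary counts as success.** For k independent tests it is 1 − 0.95^k. The correlated cases come from simulating equally correlated two-sided z tests (1,000,000 draws).

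| Tests k | Independent | Corr. 0.3 | Corr. 0.5 | Corr. 0.7 |
|---|---|---|---|---|
| 3 (one per domain) | 1 − 0.857 = 14.3% | 13.7% | 12.5% | 10.9% |
| 5 (fat % and lean % as exact complements) | 1 − 0.774 = 22.6% | 20.9% | 18.3% | 14.9% |
| 6 (all listed metrics plus LESS) | 1 − 0.735 = 26.5% | 24.2% | 20.7% | 16.4% |

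The body metrics describe the same body and will be correlated, so 26.5% is close to an upper value for six tests.

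**3. If all primaries must succeed.** The error rate does not exceed 0.05. With 80% power for each test, joint power under independence is 0.8^3 = 51% for three tests and 0.8^6 = 26% for six. Positive correlation raises these figures, to at most 80%.

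**4. The plan's own sample size.** For a repeated-measures interaction with two time points, the noncentrality is f²·N·2/(1 − rho), with 1 and N − 2 degrees of freedom.
- rho = 0.6: 0.0625 × 28 × 2/0.4 = 8.75. Power is 81%, and 28 is the minimum N.
- rho = 0.5: 0.0625 × 28 × 2/0.5 = 7.0. Power is 72%, and N = 34 would be needed.
- ANCOVA formula with f = 0.25: noncentrality is 0.0625 × 28 = 1.75. Power is 25%.

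So 28 is recovered only under an assumption the protocol does not state. That is a separate matter. What counts here is that the calculation uses one unsplit alpha.

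**5. Cost of correcting the primaries instead.** These figures are for the first Holm step, with rho = 0.6 assumed.
- Six tests: alpha = 0.05/6 = 0.0083. Power at N = 28 falls from 81% to 55%, and 80% power needs N = 44 (54 if rho = 0.5).
- Three tests: alpha = 0.05/3 = 0.0167. Power is 66%, and 80% power needs N = 38.

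These figures are illustrative. The misplaced correction does not depend on them.

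**The case against.** **No success rule is written.** A reader might infer that each of six primaries is tested at an unadjusted 0.05 and that any one would carry the claim. No sentence says so. The hypothesis closing the Introduction speaks of improvement across the outcomes together and can be read as requiring all of them, in which case there is no inflation. This stands: the defect is an undefined rule, not a declared any-one rule. It does not rescue the plan, because neither rule is stated and the joint reading does not match the sizing.

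**Six is a reading, not a designation.** The protocol names three primary items. The metrics come from a list of what the device quantifies, introduced as examples. This stands too, so the three-domain figure belongs beside the six-variable one.

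**The singular primary outcome in the sizing may not be a contradiction.** The sentence mainly contrasts primary with secondary results, and sizing on one of several primaries is incomplete rather than impossible. That is fair. It does show which outcome the authors had in mind.

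**The trial is modest in its claims.** The design section limits causal interpretation, the Limitations mention feasibility data, the Conclusion speaks of preliminary evidence, and intervals are promised for all outcomes. This softens the consequence. However, the label exploratory is applied only to the secondary results, and Practical implications expects evidence of effectiveness.

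**Conclusion.** The point holds. The only multiplicity control sits on a one-member family and has no effect, and the primary set has one alpha of 0.05 with no split, order or success rule. Both facts follow from the text without any assumption.

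The size does depend on assumptions. If any significant primary counts as success, family-wise error is about 14% for three independent tests (about 11% at correlation 0.7). For six tests it runs from about 16% at correlation 0.7 to 26% at correlation 0. If all must succeed, there is no inflation, but 80% power does not apply to the joint claim.

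The documents do not support quoting 26.5% as the trial's error rate, because that needs six endpoints, independence and an any-one rule all at once. Nor do they support treating 81% or 55% power as the protocol's own figures, since both rest on an unstated within-person correlation of 0.6.

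**What to change.** Amend the Methods abstract, Sample size and participants, and Data analysis so that they agree, before any outcome data are examined.

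**Preferred option.** Name LESS as the single primary outcome at two-sided 0.05. Apply Holm across body fat %, lean mass %, total body water %, BMI, waist–hip ratio and vertical jump height (six tests). Keep lean mass % in the family unless the device output is confirmed to make it the exact complement of body fat %. This leaves the alpha used in the sizing intact and needs no extra participants or measurements. The cost is real, because body composition loses primary status although the stated aim lists it alongside landing mechanics. The registry entry should be checked and aligned with the change.

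**If body composition must stay primary.** List every primary variable by name, apply Holm across them, and restate power at the split alpha with the assumed within-person correlation written down. Stated power then falls at N = 28, or the sample size rises.

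If the intention is that all primaries must succeed, say so and give the power for that joint claim.

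Under any option, take the Holm clause out of the sentence that lists the sample-size inputs, where it now reads as part of the power calculation.
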